#### Strategies to improve adherence to interventions {11c}

Clinical research coordinator is set up to guarantee subject compliance. Drug record cards are also distributed to allow patients to record their medication status and follow-up time.

#### Relevant concomitant care permitted or prohibited during the trial {11d}

##### Concomitant treatments and forbidden drugs

1. Avoid cold and greasy foods that are difficult to digest.

2. During the period of taking the medicine, keep optimistic, and avoid getting angry.

3. People with severe chronic diseases such as high blood pressure, heart disease, liver disease, diabetes, and kidney disease should take it under the guidance of a physician.

4. Normal menstruation, sudden excessive menstrual flow, prolonged menstrual period, or oligomenorrhea, wrong menstrual period, or irregular vaginal bleeding should go to the hospital for treatment.

5. People who are allergic to this product should not use it with caution.

6. It is forbidden to use this product when its properties change, such as from solid to liquid or packing damage.

7. If you are using other drugs, please consult your physician or pharmacist before using this product.

##### Provisions for post-trial care {30}

There are no expected harms resulting from the trial. After the trial, patients will be provided with guidance on specialized treatment protocols in psychiatry.

### Outcomes {12}

#### Primary outcome measures

##### Hamilton Depression Scale (HAMD)

The HAMD is a tool developed for clinical evaluation of depression and is widely used in studies [18]. It is composed of 17 questions. Each question is scored from 1 to 4 points, where a higher score indicates severe symptoms; 0 to 7 point is normal, 7 to 17 points may have depression, 17 to 24 points definitely have depression, and more than 24 points means severe depression. Measurements are taken at the baseline, 1 week, 2 weeks, and 4 weeks after treatment.

### Secondary outcome measures

#### Traditional Chinese Medicine (TCM) Syndrome Scale

TCM Syndrome Scale is used as a measure of depression [19]. It consists of 1 primary symptom and 9 second diagnostic symptoms. The participants are required with mental depression, and need to have more than 4 other concurrent symptoms of the main symptoms at the same time, and the symptoms should last for a 4-week session. Moreover, participants are provided with symptoms of stagnation of liver qi and spleen deficiency as follows: (1) suspicious; (2) fullness of chest and thigh; (3) chest tightness; (4) easy to sigh; (5) complexion is chlorosis; (6) stomach fullness; (7) abdominal pain; (8) bloating; (9) nausea; (10) bowel; (11) loose stools; (12) foreign body sensation in the pharynx; (13) light tongue, white tongue coating; and (14) pulse string is thin or slippery. Participant who is involved with more than 5 symptoms can be diagnosed. Measurements are taken at the baseline, 1 week, 2 weeks, and 4 weeks after treatment.

#### Exploratory outcome

The urine and blood of participants are monitored to explore the mechanism of Xiaoyao pills at baseline and 4 weeks by liquid chromatograph-mass spectrometer (LC-MS) technology. Meanwhile, the total RNA is isolated from the blood sample using TRIzol (Life Technologies). Differential expression is analyzed by using the TopHat method. Gene Ontology (GO) and Kyoto Encyclopedia of Genes and Genomes (KEGG) enrichment analysis of differentially expressed genes are implemented by the Methylmion Specific PCR. And the exploratory outcomes are expected by the network pharmacology to conduct the correlation analysis with the differential genes.

#### Participant timeline {13}

Participant timeline is shown in Fig. 2.

**Fig. 2 Fig2:**
[figure not shown]
Schedule of enrolment, interventions, and assessments

#### Sample size {14}

Based on previous findings of Xiaoyao pills in the treatment of depression [20, 21], the efficacy rate of the control group and treatment group were 32.7% and 91.4%, respectively. According to rules of thumb, we use PASS software to calculate the sample size as 30 patients in the control group and 30 patients in the Xiaoyao Pills group in a ratio of 1:1 with a type I error (*α* = 0.05) and type II error (*β* = 0.1). Meanwhile, taking into account a dropout of 15%, 72 patients are recruited with another 36 healthy persons. Therefore, we calculated the sample size as 108 participants.

#### Recruitment {15}

A total number of 72 participants with mild-to-moderate depression (referred to symptoms of liver stagnation and spleen deficiency) and 36 healthy participants are recruited at the five trial sites in china. The number of registrations at each facility is monitored by the monitoring committee via electronic data capture (EDC). We publish clinical trial information through posters and WeChat public account articles. Posters are posted in various sub-centers and communities. WeChat public account articles are open to the general public. The contact information of the research center and the researchers is found in the posters and articles. At the same time, the researcher also recruits the participants in the outpatient clinic. They evaluate and recruit prospective candidates by introducing the trial to the them. The researcher conducts a face-to-face assessment of the potential participants. And the participants who meet the inclusion criteria are formally included in the clinical trial after signing the informed consent.

### Assignment of interventions: allocation

#### Sequence generation {16a}

The study adopts the method of central stratified block randomization. According to the given seed number and segment length, the random number table of 72 subjects is generated by an independent statistician using SAS 9.4 statistical software according to the ratio of 1:1 of the Xiaoyao pills group and the placebo group.

#### Concealment mechanism {16b}

In order to make the researchers and participants unable to predict the group of the next participant, we implement the allocation sequence with sequentially numbered, opaque, and sealed boxes. Drugs are put into medicine boxes of the same size and coded in sequence. The coding of all drugs is prepared and taped by a third-party person unrelated to the trial. After the participants are officially enrolled into the group, the researchers distributed the medicine boxes to the participants. Each study center cannot know participants’ information in other centers.

#### Implementation {16c}

The allocation sequence is generated and saved by statisticians who do not participate in the clinical study. The recruitment of participants is conducted by the researchers. Researchers assess whether the participants meet the inclusion criteria. After the participants who meet the inclusion criteria sign the informed consent form, the researchers send the sealed boxes containing drugs and coded in sequence to the participants and unable to know the specific intervention of the participants.

### Assignment of interventions: blinding

#### Who will be blinded {17a}

The study uses a double-blind design and drugs are coded and packaged blind according to a generated random number table by personnel unrelated to this trial. The drugs in each group are uniformly packaged, while guaranteeing that the Xiaoyao pills and placebos are not different in appearance. The centers dispense the drugs sequentially with the assigned drug number and in the order of subject enrollment. The participants, researchers are blinded to treatment allocation. All participants are informed that they have an equal opportunity for allocation to the Xiaoyao-pills group or placebos group before enrollment. Data analysts and outcome assessors do not participate in the blinding. Clinical trial related data, such as drug types and affiliated centers, is passed to data analysts and outcome assessors after uncovering blinding. The blind bottom is kept in duplicate by the principal investigator and the sponsor after sealing, and the blind bottom could not be removed during the trial.

#### Procedure for unblinding if needed {17b}

At the end of the trial, the first-level uncovering blinding is performed after checking CRF, EDC, and signature. The groups of subjects are determined by the first-level uncovering blinding to conduct statistical analysis. After the statistics analysis, the second-level uncovering blinding is performed. Through the second-level blinding, the Xiaoyao pill group and the placebo group are determined to evaluate the drug efficacy. Unblinding is generally done at the end of the trial for statistical analysis and outcome assessment. However, in order to ensure the safety of the subjects, the blindness is uncovered in some emergency situations, such as the occurrence of a serious adverse event, unable to judge its relationship with the trial drug, whether it is overdosed, whether it has serious drug interactions with the concomitant medication, etc. When it is urgent, researchers need to know what drug to take to decide the rescue regimen. After uncovering blindness, it is necessary to record the time, reason for breaking the blindness in advance and the person performing the blind breaking, and to notify the inspector and the sponsor as soon as possible. Once the blindness is uncovered in advance, the participants should not continue to participate in the study. The data of these participants cannot be used for the efficacy evaluation analysis, but the data should still be included in the safety analysis data set. And the participants should be treated and protected in time. An emergency letter is prepared for every participant with an envelope made of thick, light tight paper. Unblinding of a single participant should not disrupt the blinding of the entire clinical trial. Emergency letters are made by a third-party person unrelated to this trial.

### Data collection and management

#### Plans for assessment and collection of outcomes {18a}

The results and baseline of all participants are collected and evaluated on Electronic Data Capture System (EDC). Assessment and collection of outcome, baseline, and other trial data are performed and recorded on EDC. All data is collected and entered into the EDC system by researchers. The system has data entry range value and character. And the system preliminarily tests the rationality of the data. After the entry, data monitoring committee checks the data quality again. During the course of this study, the sponsor performs regular on-site monitoring visits to the study centers and trains researchers in every study centers to ensure that all the elements of the study protocol are strictly followed and that the data are completed properly. At the same time, a unified case report form, HDS and TCM Syndrome Scale, should be used in every study center. Those researcher in clinical research should be relatively fixed. They should study and discuss the clinical research protocol and the manual of clinical research carefully. The way of recording and the standards of judgment should be unified.

#### Plans to promote participant retention and complete follow-up {18b}

A participant follow-up record form is set up for this study, and the follow-up of participants is managed by the clinical research coordinator (CRC). Clinical research coordinators record patients’ enrollment time, follow-up time, dose of drug, and remaining dose of drug at every follow-up time. Clinical research coordinators contact the participants to go to hospital on the follow-up day, and the research doctors evaluate the patient on the follow-up day and distribute drugs of the next phase. Every time the participants go to the hospital, they receive appropriate transportation subsidy. Before joining the project, the patient is promised to receive further treatment guidance from a specialist after the trial. If the subjects drop out of the trial or interrupt the trial, the data of the subjects is blinded with other subjects until the trial is completed. And the data of these subjects is statistically analyzed separately before uncovering blindness and finally are explained separately in the outcome part of this trial.

#### Data management {19}

The sponsor collects the paper version of case report forms (CRFs) of patient data for the proper storage as the study raw materials. All data are entered into the EDC, and any traces of entries, modifications, deletions etc. in the EDC are retained in the log showing who and when they were changed. Paper version data are input into the EDC system by two researchers in the sub-center, and double entry is adopted. The electronic data are backed up, and the backed-up electronic data are saved by another person. The sponsor checks the data again according to CRF to ensure the accuracy of the data. The sponsor arranges statisticians to complete the screening and randomization of research data. The paper-based CRF is sent to the sponsor in a safe and sealed way to ensure that they are not lost or leaked in the middle way. And all the paper-based CRF forms and the subjects’ information in EDC system are properly kept by the sponsor.

#### Confidentiality {27}

All patients’ data are kept confidential and not disclosed. Only study physicians granted authority by the sponsor have access to the EDC by account number and password and can only enter and review patient data at their site. The statistician and sponsor have access to the data for all participants. The sponsor checks the entered data regularly to ensure confidentiality. Patients’ data are stored in raw medical records at each hospital and anonymized stored in EDC for at least 5 years. Participants are allocated an individual trial identification number and participant’s details are stored on a secure database. Anonymized trial data cannot be shared with other researchers to enable international prospective meta-analyses.

#### Plans for collection, laboratory evaluation, and storage of biological specimens for genetic or molecular analysis in this trial/future use {33}

After signing an informed consent form, patients are given a baseline blood sample and retention urine sample, in which the blood routine, liver, and kidney function and urine routine are safety evaluation indicators. Meanwhile, a portion of blood samples are used for DNA methylation detection and a portion of urine samples are used for metabolomics detection. These blood and urine tests are performed again when the patient is out of the group.

Blood and urine samples are stored properly in −80°C and not be used by any other route than the study. Meanwhile, the existing as well as further sample specific studies will be conducted with ethics committee approval. If there are any remaining research specimens, biological specimens will be allowed to be used for future research in the case of reapplying for ethical approval.

### Statistical methods

#### Statistical methods for primary and secondary outcomes {20a}

Investigators establish the electronic case into the EXCEL form when making follow-up observations by interviewing the participants. Paper is entered into a database by those investigators in order to ensure data validity. All analyses are performed using SPSS software version 21.0. Differences are considered to be statistically significant for two-sided *P*<0.05. Comparisons between groups are conducted by using an analysis of covariance (ANCOVA). The significance of the cure rate, improvement rate, and unhealed rate differences between the groups are compared using ridit analysis and chi-square test.

#### Interim analyses {21b}

Security monitoring follows through the study at all times. Adverse events are reported immediately to the principal investigator, who is required to report them to the clinical trial monitoring committee within the prescribed period of time, depending on the severity. The clinical trial monitoring committee decide on a case by case basis whether to terminate the study.

No efficacy interim analysis is set up in this study.

#### Methods for additional analyses (e.g., subgroup analyses) {20b}

There will be no subgroup analysis based on gender for example or mile or moderate depression.

#### Methods in analysis to handle protocol non-adherence and any statistical methods to handle missing data {20c}

Participants with missing primary or secondary outcome data are excluded.

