### Criteria for discontinuing or modifying allocated interventions {11b}

#### Shedding criteria

Cases that have been enrolled but do not complete the clinical protocol should be considered drop outs in the following circumstances:

1. Patients withdrew from the trial on their own;

2. Lost to follow-up;

3. Poor compliance;

4. Because some diseases are considered by the study physician to be amenable to withdrawal from the trial.

The case should be explained. If the baseline pharmacodynamic data are available, the results of the last major outcome can be transferred to the final result for statistical analysis, and the research records should be kept for reference.

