#### Rejection criteria

Cases that have been enrolled but meet one of the following should be removed:

1. Cases were incorrectly diagnosed and incorrectly included;

2. Met the exclusion criteria;

3. One medication was not used;

4. Without any test record;

5. Due to the use of some prohibited medication, it was not possible to evaluate drug efficacy.

Rejected cases should state the reason, and their original medical records should be retained for statistical analysis of efficacy.

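### Dropouts are subject to two contradictory, unranked rules (exclusion or optional carry-forward), and a third instruction to analyse them separately is reconciled with neither

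*Protocol article*

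**What the plan says.** The protocol article speaks to patients with incomplete data in three places.

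- Section {20c}, on non-adherence and missing data, gives one sentence: "Participants with missing primary or secondary outcome data are excluded".
- The Shedding criteria under {11b} first define the group: "Cases that have been enrolled but do not complete the clinical protocol should be considered drop outs in the following circumstances". The circumstances are withdrawal by the patient, loss to follow-up, poor compliance and withdrawal judged appropriate by the study physician. Where baseline data exist, "the results of the last major outcome can be transferred to the final result for statistical analysis".
- Section {18b}, on retention, takes up those who drop out or interrupt the trial and says that "the data of these subjects is statistically analyzed separately before uncovering blindness and finally are explained separately in the outcome part of this trial".

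Two further rules bear on who enters the efficacy analysis. For participants unblinded early, {17b} says: "The data of these participants cannot be used for the efficacy evaluation analysis". The Rejection criteria under {11b} remove certain enrolled cases, yet say that "their original medical records should be retained for statistical analysis of efficacy".

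HAMD is measured at baseline and at weeks 1, 2 and 4 ({12}). No visit is named as the primary time point. Section {20a} compares groups by ANCOVA without listing covariates.

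**The concern.** An analyst who follows {20c} leaves a dropout out of the efficacy comparison. An analyst who follows the Shedding criteria may keep the same person in, with an earlier score standing as the final one. These are different analysis sets and can give different estimates. This is a contradiction between printed rules, so it is not a detail that a statistical analysis plan would be expected to supply.

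The wording on carry-forward is permissive, which leaves the choice to whoever runs the analysis. Under {17b} the first level of unblinding reveals the grouping before the statistical analysis starts, and nothing in the document requires the choice to be made earlier.

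Both rules also have known weaknesses. Exclusion selects randomised patients on something that happened after randomisation. Carry-forward treats a week-1 or week-2 score as if the patient's course had stopped there.

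**Working it through.** **1. The rules side by side**

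| Patient | {20c} | Shedding criteria | {18b} |
|---|---|---|---|
| Lost after week 2, baseline present | Excluded | Week-2 score may stand as the final result | Analysed separately, before unblinding |
| Attends every visit, poor compliance | Kept, nothing is missing | Counted as a dropout | Set apart, if dropout has the same meaning there |
| HAMD complete, one TCM score missing, still in trial | Excluded on a literal reading | Does not apply | Does not apply |

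In the first row, exclusion and carry-forward cannot both hold for the main comparison. The separate analysis can coexist with exclusion. It sits less well with carry-forward, because an analysis done before unblinding is not a comparison between arms. The second row shows that {20c} and {18b} do not always select the same people either.

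**2. Number affected**

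The dropout allowance in {14} reproduces: 30 / (1 − 0.15) = 35.3, rounded up to 36 per arm, or 72 in total. At 15% dropout, 72 × 0.15 = 10.8, so about 11 patients are affected and about 61 remain.

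**3. Illustrative size**

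The document gives no HAMD standard deviation, time course, arm-specific dropout rate or dropout cause. Everything in this step is assumed.

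*Set-up A.* Placebo means are 24, 22.5, 21 and 18 at baseline and weeks 1, 2 and 4. The active arm is lower by 0, 0.75, 1.5 and 3. SD is 5, the correlation between visits is 0.6, and dropout occurs after week 2. The analysis is baseline-adjusted ANCOVA on week 4. The true difference is −3.

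With fully random dropout, complete-case bias is zero. Carry-forward bias can be checked by hand. It equals (active rate × active change still to come) − (placebo rate × placebo change still to come). The remaining change from week 2 to week 4 is 19.5 − 15 = 4.5 (active) and 21 − 18 = 3 (placebo).

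- 15% / 15%: 0.15 × 4.5 − 0.15 × 3 = +0.225, estimate about −2.78
- 8% active / 22% placebo: 0.08 × 4.5 − 0.22 × 3 = −0.30, estimate about −3.30
- 22% active / 8% placebo: 0.22 × 4.5 − 0.08 × 3 = +0.75, estimate about −2.25

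The simulation gave −2.78, −3.31 and −2.25. For other mechanisms it gave:

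| Dropout mechanism (active / placebo rate) | Complete case | Carry-forward | Difference | Model using earlier visits |
|---|---|---|---|---|
| Poor week-2 score, both arms (15% / 15%) | −2.99 | −2.77 | 0.22 | −2.99 |
| Same (8% / 22%) | −2.73 | −3.58 | 0.85 | −3.00 |
| Same (22% / 8%) | −3.29 | −2.00 | 1.29 | −3.02 |
| Poor unseen week-4 score (8% / 22%) | −2.28 | −3.03 | 0.75 | −2.33 |
| Poor scorers leave active, improvers leave placebo (15% / 15%) | −3.67 | −1.90 | 1.77 | −2.98 |

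*Set-up B.* Residual SD is 6 and visit correlations are 0.5 to 0.65. Placebo dropout is driven by the week-2 score and active dropout is random.

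- 15% / 15%: complete case −2.52, carry-forward −3.06, difference 0.54
- 10% active / 20% placebo: complete case −2.16, carry-forward −3.50, difference 1.34

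Other choices for the details that Set-up B leaves open gave −2.43 against −3.49 in the second case, a difference of 1.06.

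**The case against.** A reader might infer that three mutually incompatible rules are in force and that each one biases a week-4 comparison. The documents do not support that reading.

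- **Three rules.** Section {18b} asks for a separate analysis and report. It does not say that dropouts leave the main comparison, and it is not an estimator of the treatment effect, so it cannot itself bias one. The direct conflict is between {20c} and the Shedding criteria, and the latter permit carry-forward without requiring it.
- **Each one biases.** Complete-case analysis was unbiased under random dropout and nearly so under balanced dropout driven alike in both arms. Carry-forward was close to the truth at 15% / 15% in Set-up B.
- **Week 4.** It is the last visit, but it is never named as primary.
- **Size.** The larger differences need unequal rates or unlike causes, and the plan states only 15% overall. With SD 6 and 30 per arm, the standard error is about 6 × √(2/30) = 1.55, so a shift of 0.54 is about a third of one standard error.
- **Deciding the result.** The planning rates in {14} give about 10/30 against 27/30 responders. Counting 6 placebo dropouts as successes and 6 active dropouts as failures gives 16/36 against 27/36, chi-square p about 0.008. This concerns responders and not mean HAMD, but the document's own figures do not show that the rule would decide the trial.
- **Missing TCM score.** The sentence in {20c} may mean exclusion only from the analysis whose outcome is missing.
- **Stakes.** The trial is called exploratory in {8}.

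All of these limits stand. They reduce the claim about size. None removes the conflict between exclusion and carry-forward, and the ambiguity over the TCM score is itself a reason to reword {20c}. Nor does anything suggest that the sponsor intends to choose a rule after seeing results. The text merely leaves that open.

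**Conclusion.** The point holds as a contradiction about who is analysed. For the same dropouts, {20c} excludes and the Shedding criteria permit carry-forward. No order is given, and {18b} is not reconciled with either. This conclusion needs no assumption beyond the printed text.

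Bias is a possibility under either main rule, not a certainty. In most simulated cases where score-related dropout differed between arms in rate or cause, the rules lay roughly 0.5 to 1.3 points apart on an assumed 3-point effect. The deliberately extreme case of opposite causes gave more, and balanced dropout gave about 0.2. These figures rest on assumed means, SDs, correlations, rates and mechanisms, so they illustrate the risk and do not predict it.

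**What to change.** State one primary rule by amendment before any unblinding.

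- Name the primary time point, for example week 4.
- Analyse all randomised patients with a baseline HAMD in their assigned group. Use all observed HAMD values at weeks 1, 2 and 4 in a mixed model for repeated measures, adjusted for baseline HAMD. Align the ANCOVA sentence in {20a} with this.
- Delete carry-forward from the Shedding criteria, leaving the definition of a dropout in place.
- Delete from {20c} the exclusion for a missing secondary outcome.
- Keep complete-case analysis as a sensitivity analysis.
- State in {18b} that the separate summary of dropouts is descriptive and does not remove them from the main comparison.
- Reconcile the efficacy-set statements in {17b} and the Rejection criteria with this rule. Only the use of the data is at issue, not how those patients are managed.

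The mixed model is one sound choice. The contradiction itself needs only one declared rule. The model does not cure every case: where dropout depended on the unseen week-4 score at unequal rates, a model using the earlier visits gave −2.33 for a true −3. Its recovery of about −3.0 in the other cases reflects dropout that was simulated from observed scores.

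The cost is amendment wording and slightly more analysis work. The HAMD visits are already scheduled, so no new data are needed.
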